**Fig. 4 Fig4:**
[figure not shown]
Phases of SAIA-TB study implementation

#### Intervention phase

Clusters will begin the *intervention phase* in waves, starting every 3 months. Each cluster will receive a 3- to 4-day orientation from the study team and district health authorities on SAIA-TB components. Orientation will include practice with populating and interpreting the TCAT, developing process maps of current TB and TPT patient care pathways for screening, evaluation, diagnosis, and management, and engagement in their first CQI meeting whereby they identify, prioritize, and define their first micro intervention. Subsequently, district TB supervisors, together with study personnel, introduce SAIA-TB to intervention health facilities over a 2-day period. Within each local municipality, SAIA-TB is introduced to all facilities together, and then independent facility visits will be conducted. Facility teams receive bi-weekly supervision visits by study personnel and district supervisors for the first month, followed by monthly visits throughout the remainder of the 18-month intervention phase, consistent with most adaptations of SAIA globally.

#### Maintenance phase

During the final 12-month period, SAIA-TB will have a *maintenance phase*, whereby monthly visits will continue by district authorities without study personnel to evaluate SAIA-TB’s sustainability with moderate resource investment.

It is expected that SAIA cycles will continue to occur monthly, with an average of 12 SAIA cycles per year per facility. A SAIA core component that will be maintained in SAIA-TB is provision of a flexible clinic support fund to address equipment needs for TB management (scales, some transportation costs for patients, etc.) as well as to support smaller workflow modifications, which will continue throughout both the intervention and maintenance periods. During monthly visits, facility staff participating in the intervention will complete questionnaires measuring drivers of SAIA-TB and participate in facilitation of process mapping, supportive clinical consultations, and systems engineering discussions.

### Study setting and eligibility criteria

#### Study setting

The Eastern Cape has the highest burden of TB nationally, with a TB incidence of 692 per 100,000 people, and Sarah Baartman district has the highest incidence in the country with 1022 cases per 100,000 [21]. The co-infection TB/HIV rate is 41% among patients with drug-sensitive TB and 62% among those with drug-resistant TB in the Eastern Cape [52]. The Sarah Baartman district has an average household size of 3.42 people per house and 9% of individuals living in informal dwellings. Over 77% of individuals have access to flush toilets, with 58% being female headed households and 6% being child headed households. There is a youth unemployment rate of 31% for individuals 15 to 34 years and an overall unemployment rate of 25% [52].

#### Eligibility criteria

This study will take place in four local municipalities within the Sarah Baartman district, Eastern Cape, South Africa (Fig. 5). Services for TB across South Africa are primarily provided through the public sector, and all proposed study clinics are public. Study clinics are evenly split across four local municipalities in Sarah Baartman district—Ndlambe, Sundays River Valley, Kou-Kamma, and Kouga (Table 1). These local municipalities were chosen in partnership with district of health officials for their heterogeneity in populations, proximity to Gqeberha (within 2 h’ drive to where the study office is located), patient volume (at least 4500 outpatient visits in 2022), rurality (mix of rural, semi-rural, semi-urban), and staffing mixture. Each clinic has at least two professional nurses, one or two pharmacy technicians, a data clerk, and a social worker, as well as multiple community health workers who are clinic-based or part of ward-based outreach teams.

**Fig. 5 Fig5:**
[figure not shown]
Africa, with Eastern Cape, South Africa, highlighted and Sarah Baartman district map with study locations

**Table 1 Tab1:** Sarah Baartman district statistics including area, population density, and population by local municipality

	Sarah Baartman District	[name] LM	Blue Crane Route LM	Makana LM	Ndlambe LM	Sundays River Valley LM	Kouga LM	Kou-Kamma LM
Area (square km)	58,245 km^2^	28,653 km^2^	11,068 km^2^	4376 km^2^	1841 km^2^	5995 km^2^	2670 km^2^	3642 km^2^
Population density (no)	8	3	3	17	38	10	45	13
Population (no)	483,024	77,748	30,414	74,729	69,130	62,306	120,273	48,424

### Randomization

Clusters will be randomized without restriction into implementation waves during a meeting with provincial and district health authorities and study leadership in Eastern Cape in 2024 prior to the intervention phase. Once allocated, local municipalities will not be informed of the implementation timeframe for their wave. To limit contamination between intervention sites and sites not yet receiving the intervention, all clinics within the same local municipality will be allocated to the same cluster.

## SAIA-TB impact assessment

### Study population

All patients accessing outpatient department care services at study facilities during the study period, including those screened for TB care (TB preventive treatment or disease treatment) as part of outreach events off-site or diagnosed with TB at referral hospitals and are down-referred back to their catchment clinic, are included.

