### Outcomes

We will measure each indicator across the TB care cascade from TB screening to TB-free survival. (Table 2). Primary outcomes include the mean change in proportion of individuals (1) screened for TB disease, (2) initiated on TPT, or (3) initiated on TB disease treatment combined across all facilities during the intervention period (exposed) compared to baseline (unexposed). Primary outcomes were selected based on sensitivity to system-level improvements; they represent SAIA-TB steps that, if changed, would meaningfully alter patterns of TB-related morbidity and they are routinely collected. They are relatively easy to collect and readily understood by clinic managers and frontline staff. Indicators will be assessed monthly over the study period (including 12 months baseline, 18 months intervention, and 12 months maintenance phase).

**Table 2 Tab2:** SAIA-TB primary and secondary outcomes

SAIA-TB primary and secondary outcome variables	
**TB indicator (variable)**	**Numerator/denominator**
TB screening^a^	*#screened with WHO symptom screen* # target population
TB evaluation	*# receiving a diagnostic evaluation (GXP/LAM)* # positive screening
TB diagnosis	*# diagnosed with TB (GXP/LAM/clinical)* # who completed a diagnostic evaluation
Linkage to care for TPT^a^	*# initiating TPT* # negative diagnostic evaluation + eligible for TPT
Linkage to care for TB disease^a^	*# initiating TB treatment* # positive diagnostic evaluation
Successful TPT outcome	*# completing TPT* # initiating TPT
Successful TB outcome^b^	*# cure or complete treatment for TB disease* # initiating TB treatment
TB-free survival	*# TB-free (CXR/GXP) 12 months* *after initiating TPT or TB disease treatment* # successful outcomes for TPT or TB disease

*CXR* Chest x-ray, *GXP* GeneXpert, *LAM,* Urine lipoarabinomannan

^a^Primary outcome variable

^b^WHO definition

Secondary outcomes include the additional TB cascade indicators (TB evaluation, diagnosis, treatment outcome, and TB-free survival); however, some of these are more dependent on a mix of individual-level factors (i.e., adherence to medication) (Table 2). These indicators are clinically important and can be affected at a system-level. Outcomes will be assessed for all patients receiving care, as well as assessed by important sub-groups, such as by HIV status, age (under 5 years), and local municipality (cluster).

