### Power and sample size

Power calculations are based on the primary outcome: mean change in proportion of individuals who complete screening for TB. TB screening was selected as the primary outcome as existing South African guidelines call for TB screening to be routinely implemented in outpatient services, and it is where the largest gap in the TB care cascade is currently. In a stepped wedge study, exposed and unexposed observation periods take the place of “arms” in parallel cluster trials. Outcomes (TB screening, TPT initiation, and TB treatment initiation) at baseline have been estimated to be 39% of eligible individuals screened for TB, 31% eligible individuals initiating TPT, and 70% eligible individuals initiating TB treatment per preliminary and national data (unexposed) [5, 23, 25]. We need a sample size of 978 individuals screened per cluster per time period to have 99% power (alpha = 0.05, and intracluster correlation of 0.01) to detect down to a 5% difference of proportion. Therefore, each cluster, over the course of all 5 time periods, needs to screen 4890 individuals. With four clusters, that will produce a total sample size of 19,560. Power calculations were completed using the Pass power analysis and sample size statistical software [54].

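### Off-site people enter the study population because they were screened, so if outreach screens count in the primary screening proportion, a rise in outreach under exposure inflates it

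*Protocol article*

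**What the plan says.** The Study population section of the protocol article starts from "All patients accessing outpatient department care services at study facilities during the study period", a group defined by attendance and not by screening. The same sentence goes on, "including those screened for TB care (TB preventive treatment or disease treatment) as part of outreach events off-site", and also takes in patients diagnosed at referral hospitals and sent back to their local clinic. It does not mention people approached off-site but not screened.

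The first primary outcome in Table 2 (Outcomes) is, as printed, "screened with WHO symptom screen* # target population". The article does not say what list makes up that target population. The contrast is the mean change in proportion, "combined across all facilities during the intervention period (exposed) compared to baseline (unexposed").

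Power and sample size makes screening the outcome on which the trial is sized. It gives a baseline of "39% of eligible individuals screened for TB" and a detectable difference of 5%. It justifies the choice on the ground that "existing South African guidelines call for TB screening to be routinely implemented in outpatient services". Under Eligibility criteria, the clinics' community health workers are either clinic-based or "part of ward-based outreach teams".

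**The concern.** A proportion screened measures coverage only if people get into the denominator without reference to whether they were screened. Outpatients meet that condition. People reached off-site, as the sentence is written, do not: each adds one to the numerator and at most one to the denominator, so the group is 100% screened by construction.

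This would matter little if outreach made up the same share in unexposed and exposed time. The strategy gives some reason to think it may not. Clinics choose their own changes to raise a targeted cascade step, household contacts are a named priority group, outreach workers belong to the clinic teams, a support fund for workflow changes runs through the intervention and maintenance phases, and the Background argues for active case finding. A clinic that responds to exposure by holding more outreach events would raise the primary proportion even if the same fraction of its outpatients were screened as before. The covariates named under Data analysis do not include place of screening, and the subgroups named under Outcomes do not separate it.

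**Working it through.** **Plan's own figures.** 978 per cluster per period × 5 periods = 4,890 per cluster; × 4 clusters = 19,560. Both totals reproduce. A Hussey–Hughes variance for 4 clusters and 5 periods (39% vs 44%, ICC 0.01, two-sided alpha 0.05 assumed, normal approximation) gives power of 97.5% to 97.8%, within 2 points of the stated 99%. Nothing below depends on that calculation; it only fixes 5 points as the yardstick.

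**Inputs.**
- Clinic screening proportion p = 0.39 (Power and sample size), held constant.
- Difference of interest: 5%, read as percentage points (same section).
- Outreach share s, the fraction of the denominator that enters through outreach screening. The article gives no value, so a range is assumed, with none at baseline in the examples.

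**Outreach entrants in numerator and denominator.** The observed proportion is P = p(1 − s) + 1·s. With p unchanged and the share moving from s0 to s1, the change is

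P1 − P0 = (1 − p)(s1 − s0) = 0.61 × (s1 − s0).

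| Rise in outreach share (assumed) | Proportion screened | Change, clinic screening unchanged |
|---|---|---|
| 0% | 39.0% | 0 |
| 2% | 40.2% | +1.2 points |
| 5% | 42.05% | +3.05 points |
| 10% | 45.1% | +6.1 points |
| 20% | 51.2% | +12.2 points |

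The same in counts, per 1,000 outpatients of whom 390 are screened: 100 outreach screens give 490/1,100 = 44.5%; 200 give 590/1,200 = 49.2%.

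**Share needed for a given artefact.**
- 5 points: 0.05/0.61 = 8.2%, which is about 80 of 978 people counted, or 8.2/91.8 = about 9 outreach entrants per 100 clinic patients.
- The hypothesized 20% increase read as relative (39% to 46.8%): 0.078/0.61 = 12.8%.
- The same read as absolute (39% to 59%): 0.20/0.61 = 32.8%.

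**Outreach entrants in the numerator only.** 100 screens per 1,000 outpatients give 490/1,000 = 49.0%. Five per 100 outpatients are enough for 5 points.

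**Where the artefact is zero.** If s1 = s0, the change is 0.61 × 0 = 0. It is also zero if outreach screens are left out of the indicator. If everyone approached off-site is counted, screened or not, entry no longer depends on the outcome.

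**Other primary outcomes.** In Table 2, initiation of preventive treatment and of disease treatment have denominators taken after diagnostic evaluation. Entry through screening does not make anyone a success on those outcomes, so this mechanism does not reach them.

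**The case against.** The study population and the screening denominator are different things. The former says whose data are used across the whole cascade, while Table 2 gives each indicator its own denominator. A condensed article may properly leave the operational definition of the target population to the full protocol or analysis plan. The text also hints at a denominator fixed beforehand: the baseline is given for eligible individuals, and Step 1 names household contacts, who can be listed from index patients before anyone is screened. On that reading an off-site screen of a listed contact is a legitimate numerator event. The clause can also be read as marking a subset of clinic attenders and not as adding a group. Finally, no outreach volumes are given, the strategy is described as facility-based, the outreach teams already exist, and more outreach may be a real benefit.

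Much of this stands. It shows that the bias is conditional, that its size is unknown, and that limiting the outcome to clinic attenders alone would drop household contacts, a named priority group. It does not remove the point. The article does not merely leave a term undefined; it states an inclusion rule, and for off-site people that rule selects on the primary outcome. Under the subset reading, people who attend only because outreach screening brought them in still enter through being screened. A real gain from outreach is worth measuring, but a proportion with outcome-dependent entry cannot separate it from a changed mix of on-site and off-site screening.

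A reader might infer that the primary result will be biased, or that the trial cannot answer its question. The documents do not support that. They do not say that outreach screens enter the indicator, they give no evidence that outreach will rise with exposure, and two of the three primary outcomes are untouched.

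**Conclusion.** The point holds in conditional form. As written, the inclusion rule admits off-site people because they were screened, and nothing in the article ties the screening denominator to a list made independently of screening. If outreach screens count in the proportion and the outreach share rises under exposure, the screening outcome is inflated by 0.61 points per 1-point rise, so a rise of about 8 points would equal the whole difference the trial is sized to detect. This rests on the stated 39% holding for clinic screening throughout, on outreach entrants counting in both numerator and denominator (numerator-only counting needs fewer), and on assumed outreach volumes. With an equal outreach share in unexposed and exposed time, no false effect arises. Only the screening outcome is affected, but it is the one on which the trial is powered.

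**What to change.** State that the numerator and denominator of the primary screening outcome come from the same list, made without regard to screening status: outpatient attenders in the month, plus household contacts listed from index patients if they belong to the target population. An off-site screen of a listed person then counts. Leave people who enter only through outreach screening out of this proportion. Report outreach screening separately, as a count per clinic-month or over all people approached. Keep these patients in the later cascade steps, flagged by entry route.

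The cost is a short addition to the study population and outcome definitions and one database field. The downside is that outreach gains outside the list move to a secondary outcome. Study status reports baseline collection already under way in all 16 clinics, so the flag should be added soon; records abstracted without it may be hard to separate later.

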### Exposure definition

Facilities will be considered unexposed prior to the initiation of the intervention in their local municipality and exposed thereafter. Individuals’ exposure to the intervention will be based on the exposure status of the facility in the calendar month in which they first entered TB care (including those newly identified as eligible for TPT and TB treatment and those already on TPT or TB treatment).

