**Methods:**

This stepped-wedge cluster randomized trial will evaluate the effectiveness of SAIA on TB (SAIA-TB) cascade optimization for patients with TB and high-risk contacts across 16 clinics in four local municipalities in the Sarah Baartman district, Eastern Cape, South Africa. We hypothesize that SAIA-TB implementation will lead to a 20% increase in each of: TB screening, TB preventive treatment initiation, and TB disease treatment initiation during the 18-month intervention period. Focus group discussions and key informant interviews with clinic staff will also be conducted to determine drivers of implementation variability across clinics.

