### Data analysis

Intervention analysis for primary outcomes will include generalized linear mixed modeling comparing study outcomes between exposed and unexposed times for outcomes described in Table 2 [31, 55]. Models will account for clustering by local municipality and will assess the impact of adjustment for patient-level covariates (i.e., age, sex, HIV status, and comorbidities) as well as clinic-level covariates (i.e., patient volume, staffing levels) and time (months since study initiation). We will assess missing data for randomness and employ multiple imputation, if possible [56, 57]. Additionally, we will assess outcomes among all individuals, including patients lost to follow-up, following an intent-to-treat principle [58–60]. Secondary analyses will test for interaction between exposure and time (temporal and time-to-exposure) to avoid a bias estimate of treatment effect [31]. We will also conduct a controlled, segmented time-series analysis incorporating monthly clinic-level estimates from the entire study period (segmented into 12-month baseline, 18-month intervention, and 12-month maintenance phases). This secondary analysis will allow us to fully use available data to assess intervention impact, address both serial and intra-class correlation, and assess temporal patterns in study outcomes [55, 58].

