#### Maintenance

We will measure the extent to which SAIA-TB is maintained over time at the organizational (i.e., facility) level. This will be measured as the proportion of facilities continuing to implement the intervention as designed. We will describe the proportion of local municipalities (clusters) and facilities continuing to implement SAIA-TB at 6 and 12 months post-intervention (target: > 90% at 6 months, > 75% at 12 months). Continued maintenance is defined as holding monthly SAIA-TB meetings. We will also evaluate maintenance through in-depth interviews and focus group discussions with district and facility staff on perspectives of determinants of sustained implementation or barriers to maintenance at the end of the maintenance phase as described above.

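### Exposure is open-ended in one section and limited to the 18-month intervention phase in another, so the months that enter the primary model are not settled

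*Protocol article*

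**What the plan says.** All references are to the protocol article.

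- **Exposure definition.** "Facilities will be considered unexposed prior to the initiation of the intervention in their local municipality and exposed thereafter". A patient's exposure is "based on the exposure status of the facility in the calendar month in which they first entered TB care". Neither rule ends exposure when the intervention phase ends.
- **Data analysis.** The primary generalized linear mixed model is described as "comparing study outcomes between exposed and unexposed times". The months to be included are not listed. Time enters as months since study start, with no functional form given.
- **Outcomes.** The primary outcomes are changes in proportions "combined across all facilities during the intervention period (exposed) compared to baseline (unexposed". Here the label exposed belongs to the intervention period alone.
- **Abstract, Methods.** The hypothesised 20% increases are to occur "during the 18-month intervention period".
- **SAIA-TB trial design.** Each facility has at least 12 months of baseline, 18 of intervention and 12 of maintenance.
- **Maintenance phase.** In the last 12 months, "monthly visits will continue by district authorities without study personnel". The Maintenance section, under implementation drivers, measures continuation "at 6 and 12 months post-intervention", so it treats those months as lying after the intervention.

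**The concern.** The word exposed has two meanings, and the primary model is specified by that word. An analyst who follows Exposure definition would code the 12 maintenance months like the 18 supported months. One who follows Outcomes would not. Both would be following the article, and the choice could be made after the data are seen.

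The two data sets answer the same question only if the effect is unchanged in maintenance. Whether it is sustained is what that phase is meant to find out, so coding both phases with one coefficient assumes the answer. If the effect fades, the pooled coefficient is not the intervention-period effect, and the direction of the error depends on how calendar time is modelled.

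**Working it through.** **Inputs from the article.** Four clusters, starts 3 months apart (Intervention phase); 12, 18 and 12 months of baseline, intervention and maintenance (SAIA-TB trial design); baseline screening 39%, 5 periods, 978 per cluster-period (Power and sample size).

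**Assumptions.** Baseline is exactly 12 months for the first wave, each cluster is followed through its own maintenance phase, and all cluster-months weigh the same. The model is approximated on the proportion scale. The share *r* of the effect retained in maintenance is not given, so a range is shown.

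**Plan's own figure.** 978 × 5 = 4,890 per cluster, and 4,890 × 4 = 19,560. Both agree with the article. They rest on five periods, with no separate allowance for maintenance, so they do not depend on how maintenance is coded.

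**Calendar.**
- Unexposed: 12 + 15 + 18 + 21 = 66 cluster-months.
- Intervention: 4 × 18 = 72.
- Maintenance: 4 × 12 = 48.
- Total: 186. Exposed under the literal rule: 72 + 48 = 120. Maintenance share: 48/120 = 40%.
- If all follow-up stopped at month 42, maintenance would be 12 + 9 + 6 + 3 = 30 of 72 + 30 = 102 exposed cluster-months, or 29%.
- The last unexposed month is 21 (wave 4) and the first maintenance month is 31 (wave 1). No maintenance month has a concurrent unexposed cluster.

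**Effect of pooling.** Set the effect to 1 in intervention months and *r* in maintenance months, then take the least-squares coefficient of a single exposed indicator with cluster effects. It equals 1 + *w*(*r* − 1), where *w* is the weight that falls on the maintenance months. On this calendar *w* = 0.40 with no time term, −0.16 with month effects and −0.54 with a linear month term. The weight is negative under time adjustment because maintenance months have no unexposed comparator. They inform only the time trend and the cluster levels, so a fall in maintenance is read as a falling trend and the exposure coefficient rises to compensate.

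| Effect retained (*r*) | No time term | Month effects | Linear month |
|---|---|---|---|
| 100% | 1.00 | 1.00 | 1.00 |
| 75% | 0.90 | 1.04 | 1.14 |
| 50% | 0.80 | 1.08 | 1.27 |
| 0% (limiting case) | 0.60 | 1.16 | 1.54 |

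Entries are the pooled estimate divided by the true intervention-period effect. With maintenance months left out, all three models return 1.00.

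**In points.** If the 20% increase is read as relative, 0.20 × 39 = 7.8 points. At 50% retained, the pooled estimate would be 7.8 × 0.80 = 6.2, 7.8 × 1.08 = 8.4 or 7.8 × 1.27 = 9.9 points.

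**Sensitivity at 50% retained** (no time term, month effects, linear). A 15-month first baseline gives 0.80, 1.07 and 1.26. A common stop at month 42 gives 0.86, 1.08 and 1.24.

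**The case against.** The strongest reply is that the article, read as a whole, already points to the narrower comparison. Outcomes attaches the label exposed to the intervention period. The hypothesis names 18 months. Data analysis gives the whole study period, with maintenance as its own segment, to a secondary time-series analysis, and describes that analysis as the one that makes full use of the data. This stands: a reader might infer from Exposure definition that maintenance months are certain to enter the primary model, and the article does not establish that. But no sentence excludes those months or limits the open-ended rule.

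A reader might also infer that maintenance is a different condition. It is not described so. Monthly SAIA cycles are expected to continue, as are district visits and the clinic support fund; what is withdrawn is the study personnel. Coding continued delivery as exposed is an ordinary stepped-wedge convention. The phase is better called one of reduced support.

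Third, the bias is conditional, and its largest values need a linear time term that the article does not state. With month effects it is 4% at 75% retained and 8% at 50%. The targets for continued implementation (over 90% of facilities at 6 months, over 75% at 12) concern holding meetings and say nothing about effect size.

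Finally, planned secondary analyses test exposure-by-time interaction and separate the maintenance segment, so fading is less likely to go unnoticed. They do not define the primary data set.

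**Conclusion.** The point holds as a contradiction between a stated exposure rule and the stated primary contrast, on which the primary model's wording does not decide. It does not hold as a claim that the primary estimate is biased. Under the literal rule, 40% of exposed cluster-months would be maintenance (29% with a common stop at month 42). That is a share of months, not of patients or of model weight.

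The consequence ranges from none, if the effect is fully sustained, to factors of 0.80, 1.08 or 1.27 at 50% retained, depending on how time is handled. It would be tempting to say that poorer sustainment inflates the reported effect. That is so only if maintenance is pooled and time is adjusted for, and the inflation is large mainly when time is linear; without a time term the effect is diluted. These figures rest on the calendar, equal-weight and proportion-scale assumptions above. The matter should be clarified before analysis but ranks below an essential correction.

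**What to change.** In Exposure definition, name three states for each facility: unexposed, intervention (first 18 months from start) and maintenance (the following 12). In Data analysis, state that the primary mixed model uses unexposed and intervention months only, or that maintenance has its own coefficient, and report the maintenance effect as a secondary estimate. Outcomes then needs no change.

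The cost is about one sentence in each of two sections. Leaving maintenance out gives up 48 of 186 cluster-months, none with a concurrent unexposed cluster. On the same calendar, with an intracluster correlation of 0.01 and 978/3 = 326 patients per cluster-month, the standard error of the exposure coefficient (in units of the outcome's standard deviation) rises from 0.0217 to 0.0223 with month effects, about 3%. It rises from 0.0151 to 0.0184 with linear time, about 22%, but the precision lost there depended on assuming a sustained effect and a straight trend. The stated 978 per cluster-period and 19,560 in total are unchanged.

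### The individual exposure rule does not fit the screening outcome or later starts, and the article defines exposed time in two ways for the primary comparison

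*Protocol article*

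**What the plan says.** Exposure definition in the Protocol article holds two rules. At facility level, "Facilities will be considered unexposed prior to the initiation of the intervention in their local municipality and exposed thereafter"; no end point is given. At individual level, exposure is the "exposure status of the facility in the calendar month in which they first entered TB care". The parenthesis after this rule names two groups: people newly found to qualify for TPT or treatment, and "those already on TPT or TB treatment". Entry to TB care is not defined further.

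Study population covers "All patients accessing outpatient department care services at study facilities during the study period", screened or not. In Table 2 (Outcomes) the denominator for screening is the "target population". TPT initiation is counted among people with a negative evaluation who qualify for TPT, and treatment initiation among people whose evaluation was positive. Power and sample size rests on screening.

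Outcomes sets the primary contrast as "during the intervention period (exposed) compared to baseline (unexposed". Data analysis describes the primary mixed model as a comparison of exposed with unexposed times and does not mention maintenance there. Maintenance appears as its own segment only in the secondary time-series analysis.

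**The concern.** Three things do not fit together.

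1. The only rule that assigns exposure to a person starts from entry to TB care. The powered outcome asks whether an attender was screened at all, so its failures are people for whom that event may never occur. Data analysis plans adjustment for patient-level covariates, so person-level records need an assignment.
2. First entry happens once and nothing resets it. Someone who entered care for TPT in baseline and is diagnosed with TB after crossover starts treatment in a clinic using SAIA-TB, yet carries unexposed status. The same holds for someone who entered in baseline and qualifies for TPT only later.
3. Exposed time has no end in one section and ends with the intervention phase in another. In maintenance, study personnel no longer take part in the monthly visits, so these months need not carry the same effect.

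At stake are the classification behind all three primary outcomes and the definition of the primary contrast.

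**Working it through.** **Inputs from the article.** At least 12 months baseline, then 18 intervention and 12 maintenance (SAIA-TB trial design); four clusters, starting 3 months apart (Intervention phase); 39% screened at baseline, 978 per cluster per period, 5 periods (Power and sample size).

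**The plan's own figure.** 978 × 5 = 4,890 and 4,890 × 4 = 19,560, as stated. A Hussey–Hughes calculation (39% against 44%, ICC 0.01, two-sided 0.05 assumed) gives about 97.5% power against the stated 99%. Neither figure depends on the exposure wording, so the sample size does not settle the question.

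**Screening.** At the stated 39%, 1 − 0.39 = 0.61 of the baseline screening denominator is unscreened and has no entry month through screening. This applies to baseline months; the share should be smaller in exposed months if screening rises.

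**Later starts.** The article does not say how often they occur. As an illustration, let f be the assumed share of intervention-phase events belonging to people who entered care before crossover, with equal monthly volume and a crude comparison. Mean pre-crossover time is (12 + 15 + 18 + 21)/4 = 16.5 months. The share of the unexposed group that is really post-crossover is 18f/(16.5 + 18f), and a true 5-point difference shrinks by that share:

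| f | misclassified share | 5 points appears as |
|---|---|---|
| 10% | 1.8/18.3 = 0.098 | 4.5 |
| 20% | 3.6/20.1 = 0.179 | 4.1 |
| 30% | 5.4/21.9 = 0.247 | 3.8 |
| 50% | 9.0/25.5 = 0.353 | 3.2 |

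The direction follows from the rule; the size follows from f, which is assumed.

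**Maintenance.** Post-start time per cluster is 18 + 12 = 30 months, so maintenance is 12/30 = 40%, or 48 of 120 cluster-months. I fitted a noise-free model with cluster and calendar-month fixed effects to 66 unexposed, 72 intervention and 48 maintenance cluster-months. The true effect was 10 points throughout the intervention phase. The effect in maintenance is assumed:

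| Effect in maintenance | Estimate, maintenance coded exposed |
|---|---|
| 100% persists | 10.0 |
| 75% persists | 10.4 |
| 50% persists | 10.8 |
| Linear fade to zero | 11.27 |
| 0% persists | 11.6 |

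Under the linear fade the simple mean over exposed months is (18 × 10 + 55)/30 = 7.83, where 55 is the sum of 10(1 − k/12) for k = 1 to 12. The model gives more than 10 because the late decline in early-starting clusters is absorbed by the cluster and month terms.

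Two remedies were compared under the linear fade. A single third level for maintenance inside the primary model gives 10.95 for the intervention phase. Dropping maintenance months gives exactly 10.0, as it must when the intervention-phase effect is constant.

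**The case against.** Much of the other side stands.

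- **Unscreened people.** A reader might infer that they have no exposure status at all. They do have one at facility level: the first sentence of Exposure definition classifies every facility at all times, and indicators are assessed monthly, so a facility-month screening proportion can be classified. What remains is that the individual rule does not fit this outcome.
- **Maintenance.** A reader might infer that maintenance is pooled with the intervention phase. The article does not settle on that: Outcomes confines the primary contrast to the intervention period, and the segmented analysis separates maintenance. What remains is a conflict with "unexposed prior to the initiation of the intervention in their local municipality and exposed thereafter" and with the model description in Data analysis.
- **People already on treatment.** A reader might infer that "those already on TPT or TB treatment" become automatic successes in the initiation outcomes. The phrase says whose exposure is assigned, not who enters a numerator. Table 2 has its own denominators, and these people need a status for the completion and survival outcomes. One clarifying sentence is enough.
- **First entry.** Fixing exposure at entry is a defensible intention-to-treat convention for later cascade steps. Because entry is undefined, someone screened negative in baseline and not eligible for TPT may not have entered care, so a later screen need not be locked as unexposed. This narrows the problem to later TPT and treatment starts.

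**Conclusion.** The concern holds in limited form. The individual rule does not fit the powered outcome and, read literally, assigns some post-crossover TPT and treatment starts to control. That bias is toward no difference; its size cannot be derived from the article, and the 4.5 to 3.2 points above rest wholly on an assumed f.

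The article also gives two versions of exposed time for the primary comparison, differing by 40% of post-start months. With a true 10-point effect, coding maintenance as exposed gives 10.0 to 11.6, depending on an assumed persistence from 100% to 0%. With full persistence the choice makes no difference. These figures show that the answer can depend on the unresolved definition. They do not predict a bias in this trial.

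**What to change.** 1. For the primary outcomes, assign exposure by the facility's status in the calendar month the step falls due: attendance month for screening, month of becoming eligible for TPT, month of diagnosis for treatment. Keep first-entry assignment as a sensitivity analysis. State how a start is credited when eligibility or diagnosis precedes crossover and the start follows it.
2. State that people already on TPT or treatment receive an exposure status for the completion and survival outcomes but do not enter the initiation denominators.
3. Reconcile Exposure definition and Data analysis with Outcomes: exclude maintenance months from the primary model and analyse them in the secondary segmented analysis. A single third level within the primary model is not enough, since it is exact only if the effect in maintenance is constant.

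The cost is mainly wording. Data sources describes TB registry data and an identifier for patients with TB. It does not show that attendance dates for unscreened people are held, so these must be confirmed as captured or replaced by facility-month counts. Repeat attendances need a robust variance, or a person-level term where records can be linked.
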